### Study design

This FTMDT-trial is an open randomized prospective and controlled study with 2 × 2 balanced factorial design. Patients eligible for the criteria will be randomized into four study groups (1:1:1:1) according to the randomized figures generated by the SPSS 16.0, after the patients signing the informed consents: (I) Laparoscopic surgery with fast track perioperative treatment and Xelox chemotherapy; (II) Open surgery with fast track perioperative treatment and Xelox chemotherapy; (III) Laparoscopic surgery with conventional perioperative treatment and mFolfox6 chemotherapy; (IV) Open surgery with conventional perioperative treatment and mFolfox6 chemotherapy.

Chinese medical insurance system ensures that, hospitalization is suitable for payment and also for patients' interest. All patients in this study will receive hospitalized chemotherapy in each cycle.

This trial has the independent "third-party" for developing the randomization.

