### Eligibility

Inclusion Criteria: patients who are 18 years and older, with pathologically confirmed colon and upper rectal cancer and signed informed consent prior to enrollment.

Exclusion Criteria: Tumors which can be resected by endoscopic mucosal resection (EMR) and endoscopic submucosal dissection (ESD), history of malignancy, bowel obstruction or intestinal perforation, evidence of metastasis through physical examination, chest roentgenogram and computed tomography of liver and pelvis, acute disease and acute attack of chronic disease, psychiatric history, spinal deformity, American Society of Anesthesiologists (ASA) score ≥ IV, mid-low rectal cancer, and pregnant woman.

Adjuvant chemotherapy will be needed for III stage or high-risk II stage pathologically established colorectal cancer. The performance status of the patients after surgery will be evaluated with the Zubrod-ECOG-WHO score, before the chemotherapy start. Patients with Zubrod-ECOG-WHO score sustain ≥ 2 within 3 months after surgery will be excluded and not have the chemotherapy.

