### Statistical analysis

#### Sample size calculation

Hospital stay is the primary endpoint. From the evidence in the researches [13,14,22-26], we estimate the hospital stay of laparoscopic and open surgery with Fast-track perioperative treatment is 6 and 8 days. Xelox chemotherapy has at most 1 hospitalization day for each cycle followed by taking Capecitabine orally at home, for a total of 8 cycles. Therefore, we calculate the hospital stay for groups I and II at 14 and 16 days. According to our previous research [27], the hospital stay of laparoscopic and open surgery with conventional perioperative treatment is 12 and 14 days. mFolfox6 chemotherapy requires at least 3 hospitalization days for each cycle, totally 12 cycles. So, we calculate the hospital stay of III and IV group is 48 and 50 days.

With the standard deviation of 6 days of mean hospitalization days, a total sample size of 218 would have a power of > 0.85 to detect a minimum reduction of 2 days in hospital stay among the 4 groups, using a 5% significance level. The III stage or high-risk II stage account for 64% of the total colorectal cancer patients [28], and these patients need the adjuvant chemotherapy according to the NCCN Clinical Practice Guidelines in Oncology-Colon Cancer Guideline 2009 (Version 2.2009) [29]. For this trial we will enroll 340 patients and have 85 patients in each group.

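### The planned means assume full chemotherapy, but about 36% of the 340 randomised will have none; neither possible analysis set gives the stated power for a 2-day difference

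*Protocol article*

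**What the plan says.** The primary endpoint is total hospital stay, surgical plus chemotherapy (Primary and secondary endpoint measures).

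Under Sample size calculation, the surgical stays come first: "we estimate the hospital stay of laparoscopic and open surgery with Fast-track perioperative treatment is 6 and 8 days", and 12 and 14 days under conventional care. Chemotherapy adds 8 days for Xelox (8 cycles of 1 day) or 36 days for mFolfox6 (12 cycles of 3 days), giving 14, 16, 48 and 50 days for groups I to IV. A single spread is given for all four groups: "With the standard deviation of 6 days of mean hospitalization days". On that basis the power claim reads "a total sample size of 218 would have a power of > 0.85 to detect a minimum reduction of 2 days in hospital stay", and the test level is put as "using a 5% significance level". The section then cites the share needing chemotherapy, "The III stage or high-risk II stage account for 64% of the total colorectal cancer patients", and concludes "For this trial we will enroll 340 patients and have 85 patients in each group".

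Under Eligibility, "Adjuvant chemotherapy will be needed for III stage or high-risk II stage pathologically established colorectal cancer". The same section keeps patients with persistently poor performance status after surgery off chemotherapy. The discontinuance criteria allow chemotherapy to be withdrawn after repeated severe adverse events.

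The Discussion names two comparisons: I and II versus III and IV for the model as a whole, and I versus II for the role of laparoscopy.

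**The concern.** The arms include the surgical approach, and Table 1 places randomisation before admission, so allocation precedes pathological staging. On the protocol's own share, about 36% of those randomised will contribute no chemotherapy days to the endpoint. The four planned means then cannot be the means of the four randomised groups, and one SD of 6 cannot describe them all.

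The other reading is that the endpoint is analysed only in patients who have chemotherapy. That fits the step from 218 to 340, but it uses up the whole inflation and leaves nothing for indicated patients who never start.

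At stake is the second objective, whether laparoscopy is an essential part of the model. It rests on a difference of 2 days, the figure for which the protocol claims power above 0.85.

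**Working it through.** **Inputs, all from the protocol:** surgical stay 6, 8, 12, 14 days; chemotherapy stay L = 8 (I, II) or 36 (III, IV) days; share with chemotherapy p = 0.64; SD 6; difference 2 days; 218 and 340 patients, 85 per group. **Assumptions:** two-sided 5% (the protocol does not give the sidedness); SD 6 within both the chemotherapy and the no-chemotherapy stratum; full chemotherapy or none; the 2-day laparoscopy effect equal in both strata. Powers are from the noncentral t distribution, except the unweighted pooled effect, which uses the normal approximation.

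**The protocol's own figures.**
- 218/0.64 = 340.6, so 340 reproduces as 218 inflated for the chemotherapy share.
- Power >0.85 at 218 does not reproduce. For 109 v 109, SE = 6 × √(2/109) = 0.813 and 2/0.813 = 2.46, giving power 0.69.
- The nearest variant tried is a four-group F test with assumed means 0/2/2/4, at 0.837. With 14/16/48/50 the F test has power about 1, but the 34-day gap between regimens drives that, not the 2 days.

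**Reading A: all 340 analysed.**
- Means: 6 + 0.64 × 8 = 11.12; 8 + 5.12 = 13.12; 12 + 0.64 × 36 = 35.04; 14 + 23.04 = 37.04.
- SD = √(6² + p(1 − p)L²), with p(1 − p) = 0.2304.
- I and II: √(36 + 0.2304 × 64) = 7.12.
- III and IV: √(36 + 0.2304 × 1296) = 18.29. With no variation at all within strata it would still be √(0.2304 × 1296) = 17.3.

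| Contrast, 2 days | SE | 2/SE | Power |
|---|---|---|---|
| I v II, 85 v 85 | 7.12 × √(2/85) = 1.093 | 1.83 | 0.44 |
| Pooled laparoscopy effect, unweighted | √[(2 × 7.12²/85 + 2 × 18.29²/85)/4] = 1.506 | 1.33 | 0.26 |

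Inverse-variance weighting of the two simple effects would raise the pooled figure to 0.50.

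**Reading B: chemotherapy patients only.**
- Expected number: 340 × 0.64 = 217.6, or 54.4 per group.
- I v II: SE = 6 × √(2/54.4) = 1.150, ratio 1.74, power 0.41.
- Pooled laparoscopy effect: 0.69.
- The protocol gives no rate of non-starting. At an assumed 5%, 10% or 20%, 207, 196 or 174 remain.

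**Fast-track v conventional, all 340.** Difference 35.04 − 11.12 = 23.92 days; SE = √(7.12²/170 + 18.29²/170) = 1.506; ratio 15.9; power about 1.

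**What adjustment recovers, all 340.**
- Additive adjustment for indication fits one average chemotherapy effect, (8 + 36)/2 = 22 days, and misses by 14 days in each regimen. Residual SD = √(36 + 0.2304 × 14²) = 9.0; SE = 9.01 × √(2/170) = 0.977; laparoscopy-margin power 0.53.
- With a regimen-by-indication interaction the residual SD returns to 6. Laparoscopy margin: SE = 6 × √(2/170) = 0.651, power 0.87. I v II: SE = 6 × √(2/85) = 0.920, power 0.58.

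**The case against.** The strongest reply is that the protocol's arithmetic already points to chemotherapy patients as the base: 218/0.64 matches 340 to within one patient, and an article may leave the formal analysis set to the full protocol. That stands. The two steps are consistent with each other, and the missing name of the set is not the fault. The fault is that the stated power holds in neither set.

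A reader might go further and infer any of the following, which the document does not support.

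- **That an SD of 18 undermines the whole trial.** It does not. The fast-track comparison keeps power about 1, and groups III and IV do not enter I v II, where the SD is 7.1. The large SD matters for a pooled laparoscopy effect, which the Discussion does not list as a planned comparison.
- **That the mixture causes the low power of I v II.** Mostly it does not. The all-randomised figure (0.44) is slightly above the subset figure (0.41), and 218 patients at SD 6 were already short of 0.85 for 2 days.
- **That early stoppers are lost.** They are not. Their total stay is shorter but observed. Only non-starters leave a chemotherapy-only set.
- **That any attrition must take the subset below 218.** The 64% refers to all colorectal cancer patients, whereas the trial excludes metastatic and endoscopically resectable tumours. At an assumed 70%, 238 would have chemotherapy and about 8% could be lost.
- **That the protocol assigns SD 6 to chemotherapy patients.** It does not name the population. That is an inference from the means and the inflation step.

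**Conclusion.** The point holds in limited form. The sample-size figures describe patients who complete all chemotherapy, about 64% of those to be randomised. Under either analysis set, power for the stated 2-day difference is below the claimed >0.85: I v II 0.44 or 0.41, pooled laparoscopy effect 0.26 (unweighted) or 0.69. The main fast-track question is safe.

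The powers rest on SD 6 within each stratum, a two-sided 5% test and the 64% share. That SD 6 fails in III and IV when all are analysed needs less: the mixture alone gives 17.3, and for shares from 50% to 80% the SD runs from 19.0 to 15.6. This should be corrected, because it concerns a stated property of the design and one of its two objectives.

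**What to change.** 1. Name all 340 patients as randomised as the primary analysis set for total stay.
2. Adjust for chemotherapy indication (stage III or high-risk stage II) with a regimen-by-indication interaction, or stratify fully by regimen and indication. Additive adjustment is not enough: about 0.53 for the laparoscopy margin.
3. Restate means, SDs and power for that analysis. At within-stratum SD 6 the figures are about 0.87 for the laparoscopy margin and 0.58 for I v II. Present them as upper limits, since non-starters and early stoppers add variance within the indicated stratum. Say openly that I v II is not powered at 0.85 for 2 days.
4. Do not present 218 as the evaluable number without an allowance for non-starters. Early stoppers keep their observed stay and are not subtracted.

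The cost is protocol and analysis wording; no extra patients are needed. The downside is that pathological stage is known only after randomisation and could be slightly affected by node yield, so the adjustment should be declared with that caveat.

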#### Economic evaluation

As one of the secondary outcomes, we would analyze the balance between the reduction of hospitalization days and the hospitalization cost, and evaluate whether or not FTMDT is a more economical colorectal disease treatment model.

#### Data collection and monitoring

All the data will be collected by assigned persons: the information of surgery and perioperative treatment will be collected during hospitalization, and the information of chemotherapy will be followed up.

A professional research associate develops regular contact between the study centers and monitors the information for each patient.

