### Primary and secondary endpoint measures

The primary outcome measure of this FTMDT-trial is the hospital stays, which is the overall hospitalization stay during treatment including both the hospital stay for the surgery and adjuvant chemotherapy.

We define the postoperative discharge day for the patients in the trial when they meet all of the discharge criteria, 1. Good pain control: NSR (Numeric Rating Scale) ≤ 3. 2. Tolerance of solid food, no need of intravenous fluid infusion. 3. Independent activities of daily living (ADL) to preoperative care level at least [18,19].

Secondary outcome measures are as follows, 1. Quality of life according to EORTC (European Organization for Research and Treatment) QLQ-C30 and QLQ-CR38 questionnaires, with the checkpoint frame, preoperation, 1 week post operation, 3-months post surgery and 6-months post surgery. 2. Chemotherapy related adverse events according to NCI CTCAE (Common Terminology Criteria for Adverse Events) Version3.0. 3. Surgical complications mainly include injury of the ureters, intraoperative transfusion, infection of incision, anastomotic leakage and readmission. 4. Hospitalization costs are calculated from the first day in hospital to the last day that adjuvant chemotherapy is finished.

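### The only stated collection period for surgical data is the hospital stay, which fast track shortens and which does not fit readmission; complications after earlier discharge can be under-recorded in groups I and II

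*Protocol article*

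**What the plan says.** In Data collection and monitoring, one sentence gives each type of data its own rule. For surgery, "the information of surgery and perioperative treatment will be collected during hospitalization"; for chemotherapy, "the information of chemotherapy will be followed up". No fixed number of days is attached to the surgical part.

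Primary and secondary endpoint measures defines the safety endpoint that depends on these data: "Surgical complications mainly include injury of the ureters, intraoperative transfusion, infection of incision, anastomotic leakage and readmission". It gives no time window. The same section sets quality-of-life assessments at "preoperation, 1 week post operation, 3-months post surgery and 6-months post surgery", but does not say that complications are recorded then.

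Sample size calculation gives the expected surgical stays. For fast track, "we estimate the hospital stay of laparoscopic and open surgery with Fast-track perioperative treatment is 6 and 8 days". For conventional care, "the hospital stay of laparoscopic and open surgery with conventional perioperative treatment is 12 and 14 days".

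Study objectives and the Discussion make safety a main question, to be answered by comparing groups I and II with groups III and IV. Study design states that the trial is open.

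**The concern.** Length of stay is the primary endpoint, and the fast-track package is meant to reduce it. If the stay is also the period over which surgical complications are recorded, the intervention shortens the observation time for its own safety endpoint. Take an infection or leak that shows itself in the second postoperative week. A conventional patient is typically still in hospital and the event is recorded. A fast-track patient has typically gone home, and nothing in the article says how the event would reach the database.

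The rule also sits badly with the endpoint. Readmission can happen only after discharge from the surgical stay, so a period that ended there could not contain it. If recording goes on beyond discharge, the article does not say how, for how long, or whether equally in all groups.

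At stake is the safety half of the first research question. The Discussion expects equal safety, and unequal recording could hide a true excess under fast track.

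**Working it through.** **Inputs from the article.** Surgical stays: 6 (laparoscopic) and 8 (open) days under fast track; 12 and 14 days under conventional care. Chemotherapy: "Xelox chemotherapy has at most 1 hospitalization day for each cycle followed by taking Capecitabine orally at home, for a total of 8 cycles"; "mFolfox6 chemotherapy requires at least 3 hospitalization days for each cycle, totally 12 cycles". Share of patients needing chemotherapy: 64%.

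**The plan's own totals.** Surgical stay plus cycles times days per cycle:
- I: 6 + 8×1 = 14
- II: 8 + 8×1 = 16
- III: 12 + 12×3 = 48
- IV: 14 + 12×3 = 50

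All four match the article, so the surgical stays are read correctly.

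**Difference in the stated period.** Mean planned surgical stay is (6+8)/2 = 7 days under fast track and (12+14)/2 = 13 days under conventional care: a gap of 6 days, ratio 13/7 = 1.86.

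**Illustration of the effect.** Assume equal true risk in all arms, all events within 30 days of surgery, recording until discharge only, and each patient staying exactly the planned time. The share recorded is F(stay), averaged over the two groups on each side. For uniform onset F(t) = t/30. For exponential onset with mean m, cut off at 30 days, F(t) = (1 − e^(−t/m)) / (1 − e^(−30/m)). The last column applies an assumed true risk of 20%.

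| Assumed onset | F(6), F(8) | F(12), F(14) | Mean share, fast track vs conventional | Ratio | Observed risk if truly 20% |
|---|---|---|---|---|---|
| Uniform over 30 days | 0.200, 0.267 | 0.400, 0.467 | 0.233 vs 0.433 | 0.54 | 4.7% vs 8.7% |
| Exponential, mean 8 days | 0.540, 0.647 | 0.796, 0.846 | 0.594 vs 0.821 | 0.72 | 11.9% vs 16.4% |
| Exponential, mean 5 days | 0.701, 0.800 | 0.912, 0.942 | 0.750 vs 0.927 | 0.81 | 15.0% vs 18.5% |
| Exponential, mean 3 days | 0.865, 0.931 | 0.982, 0.991 | 0.898 vs 0.986 | 0.91 | 18.0% vs 19.7% |

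The 30-day horizon, the onset patterns and the 20% are assumptions; the article gives none of them. With one common window for all groups, the artefactual ratio is 1.00.

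**Which components are affected.**
- Ureter injury and intraoperative transfusion happen in theatre: no effect.
- Incision infection and anastomotic leakage can appear after discharge: under-recorded more often where the stay is shorter.
- Readmission: a patient discharged earlier has more early time at risk, so if it is captured it may count against fast track.

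**Whether other contacts close the gap.** About 64% of patients return for chemotherapy, so 100 − 64 = 36% have no planned chemotherapy admission. Among those who return, planned inpatient days are 8×1 = 8 against 12×3 = 36, although both regimens span 24 weeks (8×3 and 12×2). The quality-of-life checkpoints are not stated to be limited to chemotherapy patients, but they are described for questionnaires, and none falls between 1 week and 3 months.

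**The case against.** A reader might infer that surgical data are collected only in hospital and that recording stops at discharge. The article says neither. It is a condensed account, and the full protocol may define a window. Listing readmission implies some capture after discharge. The word used for the period need not mean the surgical admission alone, since the primary endpoint counts chemotherapy stays as hospitalisation and a readmission is itself one. An associate also checks each patient's data. All of this stands, and it is why the point is about a badly fixed rule and not a proven gap. It does not remove the point: the one period that is stated varies by arm on the narrow reading (7 against 13 days on average) and on the broad one (planned totals of 14 and 16 against 48 and 50 days).

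A reader might also infer that fast track is made to look safer by design on the whole complication endpoint. The documents do not support that. Two of the five listed components cannot be affected, and readmission may pull the other way; a leak that brings a patient back could be counted there.

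Finally, the stays are planning means, not observation windows. The article does not say whether they run from admission or from operation. Discharge depends on meeting clinical criteria, so a patient with a developing complication may stay longer, which would weaken the effect. This limits the illustration, and no single ratio in the table should be read as an estimate for this trial.

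**Conclusion.** The point holds in a limited form. As written, the collection period for surgical data depends on the arm, is shortened by the intervention under test, and is not reconciled with readmission as an endpoint. Incision infection and anastomotic leakage after discharge can therefore be under-recorded in groups I and II, which bears on the safety comparison with groups III and IV in an open trial.

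The direction for these postoperative events follows from the planned stays, provided recording follows the stated period. The size does not: ratios of about 0.54 to 0.91 come from the four assumed onset patterns, with equal true risk, fixed stays and no recording after discharge. Any post-discharge capture applied equally in all groups would bring the ratio closer to 1. The documents support neither a stated amount of bias nor a claim that the whole endpoint favours fast track.

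**What to change.** Reconcile Data collection and monitoring with Primary and secondary endpoint measures. State that postoperative complications and readmission are recorded in all four groups, with or without chemotherapy, over one common window counted from the date of surgery, for example 30 days. Ascertain them at one scheduled contact after the window closes, or retrospectively at the existing 3-month quality-of-life checkpoint, with the date of each event so that the window can be applied. Use that window for the safety comparison of groups I and II with groups III and IV. If the full protocol already fixes such a window, citing it in this section is enough.

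The cost is a sentence or two in the protocol and either one short contact or a few added questions per patient. The existing associate and the 3-month checkpoint provide the means. Asking at 3 months is cheaper but brings some recall error.

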## Discussion

As we know, the surgery, perioperative treatment and chemotherapy for colorectal cancer stretches roughly to half a year at present, which means a long hospital stay for the patients and high medical resource costs.

As a result, two demand-oriented feasible methods have been brought into the colorectal cancer treatment, laparoscopic surgery and fast-track perioperative treatment.

For laparoscopic surgery, the COST Study Group trial has proved the advantages of laparoscopy for colon cancer, especially in faster perioperative recovery and shorter hospital stays, with the similar recurrence and overall survival rates to the open-colectomy group [1]. The UK MRC CLASICC Trial also demonstrated that laparoscopy-colectomy is as effective as open surgery in terms of oncological outcomes [30]. For Fast-track perioperative treatment, the LAFA Study Group and ERAS Group presented a systematic evidence-based consensus review, proving that Fast Track treatment appears to be safe and can shorten the hospital stay after elective colorectal surgery [9]. All the studies above provided the feasibility and safety of both laparoscopic surgery and fast-track perioperative treatment.

However, it is important to point out that, the enhanced recovery mentioned in current study about laparoscopy and Fast-track, is confined to the short-term postoperative recovery, which only lasts 1-2 weeks perioperatively. The previous study showed that quality of life benefits due to minimally invasive laparoscopic surgery were evident only in the immediate postoperative period [31]. As a result, the long-term benefit relies on the innovative treatment model covering not only surgery but also adjuvant chemotherapy. It's significant and interesting to investigate whether it will be possible to cover the enhanced recovery over the whole colorectal cancer treatment and how it works. Consequently, combining the long-term benefit chemotherapy treatment is taken into consideration.

The NO16968/XELOXA study discovered that the Xelox chemotherapy used as an adjuvant chemotherapy for colorectal cancer become possible now, as it has a manageable tolerability profile in adjuvant setting [17]. In each cycle of Xelox chemotherapy, there is only 1 day hospital stay for intravenous Oxaliplatin and the Capecitabine intake from 1st to14th day can be done in home. And in mFolfox6 chemotherapy, each cycle needs 3 days hospital stay in China. Consequently, it can be seen clearly that the superiority of Xelox for shorter hospital stay with the similar Overall Survival (OS) to mFolfox6.

On this consideration, before this trial, [name] has been conducting an open nonrandomized prospective study comparing laparoscopic surgery with Xelox chemotherapy and open surgery with mFolfox6 chemotherapy for resectable colorectal cancer, and the interim analysis has proved that the former provides faster postoperative recovery and potentially sustained better quality of life throughout treatment [32].

In the view of the separate superiority of the laparoscopy, Fast-track perioperative treatment and Xelox chemotherapy, and the possibility of the integration of these three essential treatments in colorectal cancer, the new notion "Fast Track Multi-Discipline Treatment" (FTMDT) for the integration of these three treatments is promoted in this FTMDT trial. And this FTMDT model is supposed to substantially reduce the length of hospital stays with equal safety and effectiveness, gain the better long-term recovery outcomes, and give patients a better quality of life.

The 2 × 2 balanced factorial design for this randomized prospective controlled FTMDT study tries to answer 2 corresponding questions. The I and II groups versus the III and IV groups is designed to answer the research question "Is Fast-track multidiscipline treatment model safe and effective, compared to conventional treatment?", while the I group versus II group aims to answer "Is laparoscopy an essential component of FTMDT-trial and how important role does it play?"

It's necessary to mention that, the second question about the necessity of laparoscopy use is closely related to the treatment cost. On one hand, the use of laparoscopy itself will increase the operation cost, compared to the open operation; on the other hand, the shorter hospital stay if the laparoscopy could bring, will conversely bring the reduction of the treatment cost. It is still unknown whether laparoscopic surgery has a beneficial effect on Fast-track perioperative treatment, although the most recent studies have proved that the laparoscopic surgery with Fast-track treatment also has shorter hospital stay and enhanced recovery [22-26]. However, research has found that there is no further benefit for the laparoscopy, compared with open surgery groups, and even with the two groups both using Fast-track perioperative treatment [33-35]. And some trials are still undergoing now to try to answer the question, like LAFA-trial which is now being conducted in Netherlands [36]. Consequently, it can be assumed that, if the laparoscopy did not play the essential role in enhanced recovery and reduced hospitalization, the use of laparoscopy in the Fast-track perioperative treatment could be considered again and the extra cost by laparoscopic appliance using may save.

The LAFA-trial which is now being conducted in the Netherlands has combined laparoscopy with fast track perioperative care, which will provide the merits of fast track perioperative care and laparoscopic colectomy [36]. Additionally, in this FTMDT trial the perioperative treatment of enhanced recovery for colorectal cancer treatment has the similar principle to the ERAS Group or LAFA Group [12,36], but involves the chemotherapy into study and also has a different definition for Fast track treatment. In this FTMDT trial, the notion of Fast Track treatment, is not only limited to the perioperative care but extended to the entirety of the colorectal cancer treatment, involving surgery, the perioperative treatment and the adjuvant chemotherapy. Correspondingly, the short-term superiority of the laparoscopic surgery and fast-track perioperative treatment, the long-term superiority of Xelox chemotherapy, may integrate together. Thereby, this FTMDT model covers the whole colorectal cancer treatment periods, makes it possible to achieve the whole process enhanced recovery and bring the economic benefits synonymously.

Concretely, at least 3 aspects of the advantage for the "Fast Track Multi-Discipline Treatment" Model are expected: 1. The whole process enhanced recovery: The FTMDT model itself covers the entire treatment processes for colorectal cancer. The patients who receive the laparoscopic surgery, fast-track perioperative treatment have enhanced short-term recovery, and can enter the chemotherapy earlier with good physical condition, and can also further earn the life quality benefits from the Xelox chemotherapy. 2. The economic benefits: The FTMDT model can substantially reduce the hospitalization stay because of enhanced recovery and convenient Xelox chemotherapy bring. The medical resources can be saved and the medical cost for colorectal cancer may decline as the result of decreased hospitalization stay. Moreover, Winterhalder reported Xelox is cost saving versus Folfox4, presenting the economic benefits of Xelox chemotherapy [37]. 3. The strengthened confidence of patients: The patients in the Fast Track Multi-Discipline Treatment arm earn the enhanced recovery, higher life quality, shorter hospital stay and the lighter economic burden, making patients the firmer faith against cancer and confidence for the further life.

In summary, this FTMDT trial gives insights into the potential merits and feasibility of the "Fast Track Multi-Discipline Treatment" model. A new guideline of whole process enhanced recovery treatment for colorectal cancer will be established according to the FTMDT model. This model will create another effective treatment pathway, bring economic benefits, and make the colorectal cancer treatment cost-saving and efficacy-gaining.

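### The group I versus II comparison has power of only about 0.41 to 0.58 for the planned 2-day difference, so a non-significant result could not show that laparoscopy is not essential

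*Protocol article*

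**What the plan says.** Study objectives asks two questions. The second is whether laparoscopy is an essential part of the fast-track model and how much it contributes. The Discussion pairs each question with a comparison. The first goes to I and II against III and IV; for the second, "the I group versus II group aims to answer" it.

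The Discussion then attaches a possible consequence to a negative answer: "if the laparoscopy did not play the essential role in enhanced recovery and reduced hospitalization, the use of laparoscopy" under fast-track care might be reconsidered and the added cost avoided. The document gives no margin, interval criterion or other rule for reaching that negative answer.

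The primary endpoint is "the overall hospitalization stay during treatment including both the hospital stay for the surgery and adjuvant chemotherapy". Under Sample size calculation, "we estimate the hospital stay of laparoscopic and open surgery with Fast-track perioperative treatment is 6 and 8 days"; eight one-day chemotherapy cycles are added, so "we calculate the hospital stay for groups I and II at 14 and 16 days". The same section takes an SD of 6 days and a 5% level, and claims that "a total sample size of 218 would have a power of > 0.85 to detect a minimum reduction of 2 days in hospital stay". It then gives 64% as the share of patients who need adjuvant chemotherapy, and 340 patients to be enrolled, 85 per group.

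**The concern.** The power statement speaks of a 2-day reduction among the four groups. In the plan's figures, 2 days is exactly the laparoscopic-versus-open difference: 14 against 16 days under fast-track care, and 48 against 50 under conventional care. A reader who accepts power above 0.85 for 2 days would treat a null I versus II result as informative. If the real power is much lower, such a result says little, and the step from no difference found to laparoscopy not being essential has no support. What is at stake is the answer to one of the trial's two stated questions, and any cost argument built on it.

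**Working it through.** **Inputs.** Difference 2 days, SD 6 days, 5% level, total 218, 64% needing chemotherapy, 340 enrolled (all from Sample size calculation); 1:1:1:1 allocation (Study design). Sidedness is not stated; two-sided is assumed.

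**The plan's own figure.** 0.64 × 340 = 217.6, so 218 is the expected number with chemotherapy, and 218/4 = 54.5 per group. With total 218, a 2-day difference and SD 6, the claimed power above 0.85 is not reproduced:

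| Reading of the claim | Power |
|---|---|
| I vs II, 54.5 per group, two-sided (one-sided) | 0.41 (0.54) |
| Laparoscopic vs open, 109 vs 109, two-sided (one-sided) | 0.69 (0.79) |
| Four-group ANOVA, largest difference 2 days | 0.27 to 0.51 |

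Values above 0.85 appear only for other targets: an ANOVA on means 14/16/48/50 (about 1.00, driven by the gap of more than 30 days between programmes), 170 vs 170 (0.87), or 218 in each arm (0.94).

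**Precision of I vs II.** SE = 6 × √(2/n); half-width = 1.96 × SE; power ≈ Φ(2/SE − 1.96).

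- n = 54.5: SE = 1.15; half-width 2.25 days; power Φ(1.74 − 1.96) = 0.41.
- n = 85: SE = 0.92; half-width 1.80 days; power Φ(2.17 − 1.96) = 0.58.

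The noncentral t gives 0.41 and 0.58 as well.

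**If the true saving is 2 days.** The chance of a non-significant result is 1 − 0.41 = 59%, or 1 − 0.58 = 42%.

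**If the true saving is zero.** The upper limit falls below 2 days with probability Φ(2/SE − 1.96), the same expression. The interval therefore excludes 2 days 41% or 58% of the time, and fails to do so 59% or 42% of the time.

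**In terms of the observed difference.** The upper limit is below 2 days only if the observed saving is below 2 − 2.25 = −0.25 day (n = 54.5) or 2 − 1.80 = 0.20 day (n = 85). With 85 per group, a result just short of significance (1.80 days) would have an upper limit of about 3.6 days.

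**Sensitivity.**

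- SD 5 to 7 gives power 0.55 to 0.32 at 54.5 per group and 0.74 to 0.46 at 85.
- One-sided 5% with 85 per group gives 0.70.
- If total stay is analysed in all 85, patients with and without chemotherapy are mixed. Assuming 8 chemotherapy days for 64%, none for the rest, and SD 6 otherwise, SD = √(36 + 64 × 0.64 × 0.36) = 7.1, half-width 2.14 and power 0.45.

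**Size needed for 85% power in I vs II.** n = 2 × 36 × (1.96 + 1.036)²/2² = 161.6, so 162 per group. The same 162 gives 85% power to exclude 2 days when the true difference is zero (one-sided 2.5%).

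**What the factorial design offers.** The laparoscopy main effect over all 340 (170 vs 170), if SD 6 also applies, has SE 0.65, half-width 1.28 and power 0.87. The laparoscopy-by-programme interaction has SE = 6 × √(4/85) = 1.30, half-width 2.55, and power for a 2-day interaction of Φ(2/1.30 − 1.96), about 0.34.

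**The case against.** The strongest reply is that the plan nowhere commits itself to the faulty inference, and on the text this is right. The sentence in the Discussion is a hedged conditional. It names no significance test, covers recovery as well as hospital stay, and sits in an argument about cost; quality of life, complications and cost are separate endpoints. A reader might infer that a non-significant result will be taken as proof of no effect, but the document does not say so. What stands is narrower: I versus II is the only comparison assigned to the question, a consequence is attached, and the stated power makes a null look informative when it is not.

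Four other strong readings also fail.

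- **That the 36% without chemotherapy are dropped.** The 64% is used only in setting enrolment; no analysis set is defined by it. Hence both 54.5 and 85 per group are shown.
- **That the interval can never exclude 2 days.** With no true saving it does so 41% to 58% of the time.
- **That leaving out groups III and IV is an error.** The question concerns laparoscopy within the fast-track model, and I versus II targets exactly that. Pooling the arms answers it only without interaction, which this trial can check only weakly.
- **That chemotherapy days merely add noise, so surgical stay should replace total stay.** Total stay is the declared primary endpoint, and the Discussion expects enhanced recovery to bring patients to chemotherapy earlier and fitter, so surgery could influence later stay. The SD of 6 is also given for the total, not for surgical stay.

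How a null is to be interpreted may also be set out in an analysis plan that is not shown. That would supply a rule, but it would not change the precision of the comparison.

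**Conclusion.** The concern holds in limited form. I versus II is a legitimate comparison for the second question, but on the plan's own 2 days and SD 6 (two-sided 5%) its power is about 0.41 on the 218 basis or 0.58 with all 85 per group, not above 0.85. A true 2-day benefit would be missed about 42% to 59% of the time, and a true absence of benefit would leave 2 days inside the interval equally often. A non-significant result must therefore not be taken as showing that laparoscopy is not essential. The figures rest on the stated SD, on two-sided testing and on a normal approximation. Across SD 5 to 7, power reaches at most 0.74. This affects what the trial may conclude, not its conduct.

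**What to change.** 1. Keep I versus II as the estimand for the second question. Report open minus laparoscopic stay with its 95% confidence interval in all randomised patients (85 vs 85), on the declared total stay, with surgical stay as a supporting analysis.
2. State the rule in advance: conclude 'not essential', as far as stay is concerned, only if the upper 95% limit is below the plan's own 2 days. Report any other non-significant result as inconclusive.
3. As further support, fit the two-way factorial model to all 340 patients. Give the laparoscopy main effect and the interaction, each with its interval. Say plainly that the interaction is imprecise (SE about 1.30 days if SD 6 applies), so the main effect does not replace I versus II.
4. Correct the power statement, or say which comparison it refers to.

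The cost is wording and analysis only, with no new patients or data. The downside is that some results will be declared inconclusive: with 85 per group and SD 6, any observed saving between about 0.20 and 1.80 days. Designing I versus II for 85% power would instead need 162 per group, that is 648 patients with chemotherapy over four arms, or about 1,013 enrolled at 64%. That shows the scale of the gap and is not proposed here.
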